## **9 Data handling and record keeping**

### **9.1 Data management and processing**

All protocol data will be captured in Case Report Forms (CRF) that will be completed for each included participant using electronic data capture. On the CRF, a reference to the source document will be provided. Instructions for completing all forms, including the CRF, used in the study will be developed.

The following data will be recorded: date of informed consent, personal data (ID, initials, date of birth), socioeconomic data, height and weight, information on health status and regarding participation in other studies, date and time of all venous and finger prick blood collections, date and time of all faecal sample collections, date and time of supplement administration, data on morbidity, lab results.

All trial data will be stored and managed within a clinical database built on the REDCap platform, an application specifically designed to collect and store clinical trial data and customised for Electronic Data Capture (EDC) in the field. Where appropriate, data entry fields will incorporate appropriate range checks. At the point of data collection, data will be entered directly into tablet computers as already done in the MRCG studies, and uploaded to the main server either immediately, or at least daily when network signal is weak. Data export options from the clinical database include CDISC ODM XML, a vendor neutral, platform independent format for interchange and archive of data collected in clinical trials. This should ensure sharing and long term validity of data. This data management system is a fully supported, externally validated (GCP compliant to 21 CFR part 11) clinical database.

Prior to the first participant enrolment a detailed trial specific data management plan (t\_DMP) will be created, reviewed and signed off by the Data Manager and the TSC. This t-DMP will outline in detail the specific procedures that will be used to ensure high quality data will be delivered for statistical analysis and future use. The t-DMP will complement the trial risk assessment and statistical analysis plan. Review of data collection tools against the protocol will occur prior to database build by the Data Manager to ensure all data is being captured, at the correct time points, and in a format conducive to the proposed statistical analysis. Site based staff will be fully trained in conducting any study assessments and subsequent completion of the CRF and a Site delegation log will be maintained. Data entry staff will be trained in the use of OpenClinica. Principles of good clinical practice will be adhered to and all training will be documented. To ensure standardisation of processes, standard operating procedures with respect to trial management, quality assurance, data management, IT & security, and statistics will be adhered to.

## **9.2 Source documents and access to source data**

The local PI will maintain appropriate medical and research records for this study in compliance with the principles of good clinical practice and regulatory and institutional requirements for the protection of confidentiality of participants. The study team members will have access to records.

The authorised representatives of the sponsor, the ethics committee(s) or regulatory bodies may inspect all documents and records required to be maintained by the investigator, including but not limited to, medical records (office, clinic, or hospital) for the participants in this study. The clinical study site will permit access to such records.

### **9.3 Protocol deviations**

A protocol deviation (PD) is any noncompliance with the clinical trial protocol, good clinical practice (GCP), or other applicable regulatory requirements. The noncompliance may be either on the part of the participant or the investigator including the study team members, and may result in significant added risk to the study participant. As a result of a deviation, corrective actions will be developed and implemented promptly.

If a deviation from, or a change of, the protocol is implemented to eliminate an immediate hazard(s) to trial participant without prior ethics approval, the PI or designee will submit the implemented deviation or change, the reasons for it, and, if appropriate, the proposed protocol amendment(s) as soon as possible to the sponsor for agreement and the relevant independent ethics committee (IEC) for review and approval.

The local PI or designee will document and explain any deviation from the approved protocol on the CRF, where appropriate, and record and explain any deviation according to the Unit's SOP.

## **10 QUALITY CONTROL AND QUALITY ASSURANCE**

Quality control will be applied to each stage of the study. We will work together with the Sponsor, through their Quality Management team (Mrs *[name]*) and Research Governance teams (led by [name]) to finalise a plan for the trial quality monitoring.

It will be the responsibility of the local PI or designated trial team member to ensure that all source documents and CRFs are reviewed for accuracy and completeness. Any correction will be accurately accounted for.

Finger prick and venous blood collection will be done by the trial nurses. Collection of all samples will be recorded on the CRF.

All Field assistants and their supervisors including trial nurses will be fully trained. Selected participants from the RCH teams will also be trained. Further refresher training will be conducted as the trial progresses. Weekly field team meetings and monthly meetings of the entire trial team will be convened in order to discuss all problems and lessons from the trial.

We will also work with the Quality and Laboratory Management teams to write a detailed Analytical Plan for the trial and appoint a study team member (likely one SO) as the Analytical Project Manager who will be responsible for overseeing and ensuring the quality of the laboratory activities for the trial.

### **10.1 Study monitoring**

A risk-based monitoring plan will be developed with the MRCG Clinical Trial Support Office prior to study starting. This will describe monitoring frequencies and content of Site Initiation, Interim Monitoring and Close-out Visits.

## **11 Ethical considerations**

This study is conducted in accordance with the principles set forth in the ICH Harmonised Tripartite Guideline for Good Clinical Practice and the Declaration of Helsinki in its current version (see appendix), whichever affords the greater protection to the participants.

### **11.1 General considerations on human subject protection**

Study participants will be young children and the study protocol will be explained to their mothers/guardians orally in the presence of an independent witness in case they are illiterate or in writing. No children will start any study specific procedure before informed consent is obtained. The study investigates iron supplementation in doses specifically recommended for this age group by the WHO. Participants will not get any remuneration but will have free basic medical care for the duration of the study.

#### **11.1.1 Rationale for participant selection**

Young children, together with pregnant women, are the two most affected population groups in relation to anaemia and iron deficiency anaemia, and the groups for which better iron supplementation strategies are required.

In pregnant women the main problems of current iron supplements are the gastrointestinal side-effects such as nausea, abdominal cramps, heartburn and constipation (15), which affect compliance with treatment. Our future aim is to be able to also conduct a trial in pregnancy to test the hypothesis that IHAT would not be associated with these side-effects in the pregnant women. We are actively seeking funding for this.

However, in our opinion the most pressing need in relation to iron supplementation in developing countries is to find an alternative iron supplement for use in young children living in areas at risk of enteric infection. As mentioned in the Background Section, RCTs with current iron supplementation in nearly ten thousand young children living in developing countries have consistently shown that these are associated with increased infection including bloody diarrhoea (3, 6-8) and detrimental changes to the gut microbiome and gut inflammation (8, 9), further increasing the burden from enteric infection and environmental enteropathy (i.e. persistent gut damage and inflammation that leads to malabsorption), which is a major cause of growth failure in children in resource-poor environments (10, 11). Furthermore, it appears that these effects are much more relevant in those resource-poor countries where enteric infection risk is higher and in the pre-school age group since in South-African 6-11 years old children with a low enteropathogen burden, iron supplementation did not significantly affect the dominant bacterial groups in the gut or gut inflammation (53). The specific problem this proposal seeks to address relates to these effects of oral iron supplements for treating anaemia in young children. Hence, why we propose to conduct the trial in young children living in the most deprived areas of The Gambia where the risk for enteric infection is higher.

More than 70% of all children under 5 y. in The Gambia will be anaemic and in most cases this will be due to iron deficiency. The consequences of anaemia and iron deficiency include impaired neurocognitive development and immunocompetence leading to substantial loss of human potential.

Combating anaemia due to iron deficiency is a challenge due to the potential negative side-effects of iron when given to people with infections, as is extremely common in young children in The Gambia.

Specifically, we will be addressing the fact that current iron supplements increase risk of moderate-severe diarrhoea in these children, particularly in settings where risk for enteric infection is high, as we mentioned above. In the 21st century, we simply cannot accept the current view that increased risk of infectious diarrhoea in young children is normal collateral damage of oral iron supplementation in populations at high risk of enteric infection. This is a

problem of current iron supplements and we believe that IHAT will work differently for all the reasons explained in the Rationale Section of this protocol. IHAT may also offer other advantages in relation to conventional iron supplements in relation to efficiency of absorption of consecutive daily doses and systemic infection risk as explained in the Rationale Section of this protocol.

Finally, we wish to note that we believe that IHAT's main target population group, where IHAT's benefit will really outweigh its added cost over current iron supplements, are young children from resource-poor countries. This is because the main advantage of IHAT over other iron supplements relates to its intestinal safety and, as we mentioned above, young children living in areas of enteric infection risk are the main population group affected by the negative effect of current iron supplements on intestinal infection (including bloody diarrhoea) and inflammation (contributing to environmental enteropathy). Essentially, if IHAT works in the proposed trial, where it will be tested in the population group that is more responsive to the adverse effects of iron supplementation (i.e. young children at risk of enteric infection), then it will work in any other population group. But the reverse is not true, i.e. if IHAT works in adults it does not mean it would work in children, and similarly if IHAT works in older children it does not mean it would work in the young children group, since these are the subjects with the most immature gut where the microbiome is not stable and where the mucosa is more susceptible.

This is why it is crucial to conduct the trial in the young children living in some of the most deprived and infectious communities in the Gambia. Conducting the study in adults would not provide us with clinically-meaningful information about the impact of IHAT on enteric infection and diarrhoea risk, since this effect is not commonly observed in adults (possibly due to the immature gut microbiome and mucosa in young children) with iron supplementation, and would just delay further investment and the authorisation of IHAT for use in children, which would be unethical in our view. As such, we follow the recommendation of the European Medicines Agency to study medicines intended to be used in children in a paediatric population rather than inferring the information and dosages from adult trials (Regulation (EC) No 1901/2006). We appreciate that children are a more vulnerable group for the first Phase II trial of IHAT or indeed any other form of iron supplementation, but they are also the group that will most benefit from a better iron supplement. The health of all children in our study will be closely monitored as will all adverse events including all diarrhoea episodes, malaria and other co-infections. Therefore, ethically we will not be subjecting children to any unnecessary risk or, in fact, any more risk than when current iron supplements are used as per national guidelines. In the worst case scenario, IHAT will be the same as currently used ferrous sulphate or fumarate in terms of diarrhoea and other adverse events.

This study will provide the first Phase II trial data with IHAT and will enable us to obtain high-quality clinical data for its safety and efficacy in correcting IDA in children, the population group most in need of an alternative oral iron supplement. If IHAT is successful in the trial, these data will provide the evidence needed to encourage further investment so that IHAT can be implemented as a novel iron source for use in micronutrient intervention strategies aimed at children and women living in resource-poor countries and, hence, reduce the global burden of IDA.

### **11.1.2 Rationale for use of a placebo group**

We have thought very carefully about the lower threshold of Hb inclusion for all study arms and we wish to note that we are not contravening the current national guidelines, since there is no mandatory iron supplementation for this age group in the Gambia. All our prior iron intervention trials in The Gambia, Kenya and Tanzania, have used the Hb 7-11 g/dl inclusion criteria. The rationale being that Hb below 7 g/dl is the current WHO cut-off for severe anaemia in children under 59 months of age (WHO/NMH/NHD/MNM/11.1), and these children would be the ones presenting with more visible symptoms of anaemia and most likely to be automatically given oral iron treatment.

Since recent trials have demonstrated a possible detrimental effect of iron supplements in pre-school age children, there is now a strong ethical rationale for a 'no-iron' control group (i.e. placebo). It is crucial to have this placebo control group in our study, not only for determining background 'side-effects' but also, and importantly, for assessing the true treatment effect size of current iron supplementation (i.e. ferrous sulphate) in Hb levels. There have been numerous iron supplementation studies in young children in resource-poor countries, including in the Gambia, that have failed to show any decrease in anaemia prevalence with iron supplementation, and we feel it is necessary that we determine in this study if iron supplements are preventing Hb from falling further in relation to a 'no iron' (or placebo) group, which we consider to be an important positive effect, even when anaemia prevalence may not decrease for this age group due to the high demands for iron during fast growth.

It is also important to have a placebo group in this study so that we can perform an exploratory analysis and test for assay sensitivity and to determine treatment effect size with IHAT so that these data can be used to power future studies.

In the proposed study we will include only children with mild-moderate anaemia, and we will exclude any children with severe anaemia, who would be most likely identified and referred for iron treatment according to the national policy in The Gambia. The children with Hb between 7 and 11 g/dl would probably not be identified as anaemic had they not been offered screening through our study and would not have been provided with oral iron supplements. Within this

group, the children with Hb between 7 and 8 g/dl are the ones most in need of an alternative oral iron treatment, one that is both effective and safe. In any case, as we mentioned above, we will monitor very closely the Hb levels in all study arms and discontinue the study intervention and treat according to the national guidelines any children where Hb falls below 7 g/dl at any point during the study. These children will continue to be followed-up by the study clinical team at the weekly clinics. Furthermore, at the end of the study, any child who remains anaemic will be offered the standard iron supplementation according to national policy. This means that we will only be delaying treatment for the children in the placebo group by 4 months (unless they become severely anaemic during the study, in which case they receive treatment immediately).

### **11.1.3 Evaluation of risks and benefits**

There are risks associated with a large intake of iron supplements especially in areas of malaria endemicity. The dose of iron given daily in the reference arm (12.5 mg) is according to WHO guidelines for the age group children in non-malarious areas or malaria-endemic areas where it should be implemented in conjunction with measures to prevent, diagnose and treat malaria and co-infections. The iron dose in the IHAT arm (20 mg) is the bioequivalent dose, i.e. the same absolute amount of iron should be absorbed as in the ferrous sulphate arm, and because IHAT should be safer to the gut, the unabsorbed fraction should not cause detrimental effects, such as infectious diarrhoea. This dose (20 mg Fe) is still less than the new WHO recommendation for children in our 24-35 mo. age group (i.e. 30 mg, (40)). In any case, in all arms of the trial these adverse events will be closely monitored.

Additionally, we have put in place the following strategies to mitigate the risk of possible interactions between iron supplements and malaria or other co-infections:

(1) data from the Gambia over the last 5 years (medical records from the Kiang West region) shows that the peak malaria months are Oct and Nov and, therefore, we have timed the intervention period to avoid these months, (2) trained field workers will be visiting all children every day during the 12 weeks supplementation period in order to supervise the administration of the iron supplements or placebo and on these occasions they will check on the children's health status and actively look for signs of malaria and co-infections, if a child shows signs of these infections the study nurse will perform adequate tests and the child will be offered the appropriate treatment/referral to the next Health Centre. In case of a fever, a malaria rapid test will be performed and if positive the child will be treated according to national guidelines. A sick child will always be visited by a study nurse for further clinical investigations and if needed referred to the nearest Health Centre. These visits will carry on for 4 weeks after the end of the study

intervention and, during both the intervention and this follow-up period, morbidity data will be captured every other day. This is similar to what was done in the HIGH study and we do not anticipate any difficulties of implementation. Every week, the child will visit one of the study health facilities for a haemoglobin check-up and malaria RDT testing, and this will ensure that children that develop asymptomatic malaria are identified and treated according to national guidelines.

Participants will experience some transient pain during blood sampling, which will be minimised by recruiting well-trained nurses for the study.

Children will benefit from daily monitoring of their health and from immediate care in case of illness. Although the mechanism of combating iron deficiency is problematic, it is clear that iron is a key micronutrient for the development of the immune system and cognitive function in these young children.

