- Increased malaria and co-infections risk during and after oral iron supplementation; there are risks associated with a large intake of iron supplements especially in areas of malaria endemicity. The dose of iron given daily in the reference arm (12.5 mg) is according to WHO guidelines for the age group children in non-malarious areas or malaria-endemic areas where it should be implemented in conjunction with measures to prevent, diagnose and treat malaria and co-infections. We have put in place the following strategies to mitigate the risk of possible interactions between iron supplements and malaria or other co-infections: (1) data from the Gambia over the last 5 years (medical records from the Kiang West region) shows that the peak malaria months are October and November and, therefore, we have timed the study intervention periods to avoid these months so that there will be no intervention/supplementation during Oct and Nov 2017 (2) trained field workers will be visiting all children every day during the 12 weeks supplementation period in order to supervise the administration of the iron supplements or placebo and on these occasions they will check on the children's health status and actively look for signs of malaria and co-infections, if a child shows signs of these infections the study nurse will perform adequate tests and the child will be offered the appropriate treatment/referral to the next Health Centre. In case of a fever, a malaria rapid test will be performed and if positive the child will be treated according to national guidelines. A sick child will always be visited by a study nurse for further clinical investigations and if needed referred to the nearest Health Centre. These visits will carry on for 4 weeks after the end of the study intervention and, during both the intervention and this follow-up period, morbidity data will be captured every other day. This is similar to what was done in the HIGH study and we do not anticipate any difficulties of implementation. Every week, the investigators will check whether children are RDT positive. Note: according to national guidelines, all children at birth are provided with bed nets and children in the URR receive intermittent preventive treatment (IPT) of malaria and so we have not anticipated we would need to provide insecticide-treated bed nets to the study population, but we could do this is deemed necessary.

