Prior to enrolment (Day 0), which will be a maximum 4 weeks after the screening visit, eligible children will be taken back to the clinic for a finger prick to confirm absence of malaria by RDT and haemoglobin concentration by hemocue. Children will be called back in clusters of 58-60 on a Monday, Tuesday, Wednesday and Thursday. This is necessary before they can be enrolled and randomised to the study because of the time it takes to get all the screening results back from the labs for all children in that cohort (i.e. around 4 weeks). On the Friday of the same week, the list of all the children that remain RDT negative and with  $7 \leq \text{Hb} < 11$  g/dL will be sent to the

study statistician who will run the randomisation to one of the three study arms, stratified by Hb and age as described in 3.2.1., and send the list with the study IDs to the PIs that same day.

The week after, children will be taken back to the clinic again in the same cluster (i.e. either on the Mond, Tue, Wed or Thur as per their Day 0 cluster) and this will be their study Day 1 (see below).

We will enrol children in 3 cohorts (n=235 children each) that will run sequentially.

Each study cohort will be organised as follows. Each cohort will have 4 clusters (58-60 children per cluster), children in each cluster will be allocated to one of the study health facilities according to the child's compound proximity to each of the 4 study health facilities. Children in the first cluster will all have their study visits on a Monday, children in the second cluster will all have their study visits on the Tuesday, and the third cluster on the Wednesday and fourth cluster on the Thursday. Children in each cluster will also have their weekly check-ups at the study health facility on the same day of the week and would have had their Day 0 visit on the same day of the week.

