| Participant recruitment cohort 1                         | Mon 30/10/17        | Thur 04/01/18        |
| Participant recruitment cohort 2                         | Mon 05/03/18        | Thur 05/04/18        |
| Participant recruitment cohort 3                         | Mon 18/06/18        | Thur 02/08/18        |
| Local analysis of screening samples                      | Mon 30/10/17        | Fri 30/11/18         |
| Interim report submitted (M 2)                           | Fri 31/08/18        | Fri 31/08/18         |
| Milestone 2                                              | Fri 31/08/18        | Fri 31/08/18         |
| Trial Field Data Collection                       | Mon 08/01/18 | Thur 29/11/18 |
| Cohort 1 intervention                                    | Mon 08/01/18        | Thur 05/04/18        |
| Cohort 2 intervention                                    | Mon 23/04/18        | Thur 19/07/18        |
| Cohort 3 intervention                                    | Mon 06/08/18        | Thur 01/11/18        |
| AEs follow-up                                            | Mon 08/01/18        | Thur 29/11/18        |
| Local analysis of trial samples                          | Mon 08/01/18        | Fri 30/11/18         |
| Interim report submitted (M 3)                           | Fri 14/12/18        | Fri 14/12/18         |
| Milestone 3                                              | Fri 14/12/18        | Fri 14/12/18         |
| Analysis and Reporting                            | Mon 17/12/18 | Fri 29/03/19  |
| External analysis of trial samples (microbiome and NTBI) | Mon 17/09/18        | Fri 21/12/18         |
| Data queries resolved                                    | Mon 30/10/17        | Fri 30/11/18         |
| Data analysis                                            | Mon 17/12/18        | Thur 28/02/19        |
| Data monitoring committee report                         | Fri 01/03/19        | Fri 29/03/19         |
| Final project report                                     | Fri 01/03/19        | Fri 29/03/19         |
| Publication of findings submitted                        | Mon 04/03/19        | Fri 29/03/19         |
| Milestone 4 and Project End                       | Sun 31/03/19 | Sun 31/03/19  |

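### The protocol says the intervention is timed to avoid the peak malaria months of October and November, but its own timeline doses all of cohort 3 through most or all of October 2018

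*Supplement*

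**What the plan says.** All references are to the latest protocol version in the supplement, the one in which cohort 3 recruitment ends in July 2018.

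- Section 11.1.3 lists strategies against interaction between iron and malaria or other infections. The first is that "the peak malaria months are Oct and Nov and, therefore, we have timed the intervention period to avoid these months". It names no year.
- Section 1.4.1 lists the same strategy, then attaches a year: "we have timed the study intervention periods to avoid these months so that there will be no intervention/supplementation during Oct and Nov 2017".
- Appendix 1 has the row "Cohort 3 intervention | Mon 06/08/18 | Thur 01/11/18" and shows adverse-event follow-up ending on 29 November 2018.
- Section 5.1.2: "We will enrol children in 3 cohorts (n=235 children each) that will run sequentially".

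The second strategy in Sections 1.4.1 and 11.1.3 is surveillance: daily visits by field workers, a rapid diagnostic test (RDT) when a child has fever, weekly RDT, treatment or referral, and visits continuing for four weeks after the intervention. Section 1.4.1 adds that children in the region are given bed nets and intermittent preventive treatment under national guidelines.

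**The concern.** The timing statement and the timeline cannot both be true for cohort 3. Section 11.1.3 itself says that iron intake carries risk, particularly where malaria is endemic, and timing is the only one of its two numbered strategies that works by avoiding exposure. The other detects and treats. A reader of the risk-benefit section would conclude that no child takes study iron in the peak months, and the schedule does not deliver that for cohort 3.

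There is also a smaller point for the analysis. Malaria is a secondary endpoint, and infection can move haemoglobin and ferritin, which define the efficacy response. If the cohort dosed in a peak month behaves differently, a summary pooled over cohorts would not show it.

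**Working it through.** **Inputs**
- Cohort intervention windows (Appendix 1): "Cohort 1 intervention | Mon 08/01/18 | Thur 05/04/18"; "Cohort 2 intervention | Mon 23/04/18 | Thur 19/07/18"; and cohort 3, 6 August to 1 November 2018.
- Dosing: daily for 12 weeks, first dose at the Day 1 visit, with visits on Days 85 and 113 (Sections 5.1.3 and 5.1.4).
- Four clusters per cohort, starting Monday to Thursday of the same week (Section 5.1.2).
- Cohort size 235 of 705 (Section 5.1.2); allocation 1:1:1 (Section 3.1).

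**Reproducing the timeline.** The last dose is Day 1 + 83 days, Day 85 is Day 1 + 84 days, and Day 113 is Day 1 + 112 days.

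| Cohort 3 cluster | Day 1 | Last dose | Day 85 | Day 113 | October doses | November doses |
|---|---|---|---|---|---|---|
| 1 | 6 Aug | 28 Oct | 29 Oct | 26 Nov | 28 | 0 |
| 2 | 7 Aug | 29 Oct | 30 Oct | 27 Nov | 29 | 0 |
| 3 | 8 Aug | 30 Oct | 31 Oct | 28 Nov | 30 | 0 |
| 4 | 9 Aug | 31 Oct | 1 Nov | 29 Nov | 31 | 0 |

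Cluster 4 gives the Appendix 1 end dates exactly: 1 November for the intervention and 29 November for follow-up. The same rule gives 5 April and 19 July 2018 for cohorts 1 and 2, also as printed. The cohort 3 dates are therefore no typing slip. They also fit Sections 1.4.1 and 4.1, where cohort 3 recruitment ends in July 2018.

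**Overlap with the peak months**
- Per child in cohort 3: 28/84 = 33% to 31/84 = 37% of dosing days fall in October, none in November.
- Cohorts 1 and 2: no dosing days in either month.
- Children affected: 235/705 = 33%. On iron: 235 × 2/3 ≈ 157, and 157/705 = 22% of the trial.

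**The 2017 wording.** The earliest dosing date in Appendix 1 is 8 January 2018. A promise of no supplementation in October and November 2017 is met whatever the cohort 3 dates are. Section 11.1.3 carries no such limit.

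**The case against.** The strongest reply is that this is one sentence left behind when the timeline moved. In the earlier protocol versions cohort 3 ended on 14 September 2018, so the statement was true there. The revised dates are printed in the same document, and all the surveillance measures still cover cohort 3. That explains the conflict and limits its consequences, but it does not remove it: the current text asserts a protection that the current schedule does not give.

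Several stronger readings are tempting, and the documents do not support them.

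- *Season biases the comparison of IHAT with ferrous sulphate.* It should not. Each cohort is randomised as its own batch (Section 5.1.2), with the haemoglobin split at that cohort's own median and blocking within age-by-haemoglobin strata (Section 3.2.1). The arms are therefore approximately balanced within each cohort.
- *The lack of a cohort term in Section 8.2 is an error.* That section is a short summary and defers to an analysis plan to be completed before database lock, which is not shown.
- *The ethics committee and DSMB were misled.* What they were told about the timeline change cannot be seen. Only the inconsistency in the text is established.
- *Children are dosed in November.* They are not. 1 November is the last Day 85 visit, and only follow-up runs through that month.
- *Cohorts 1 and 2 are dry-season cohorts.* The protocol does not date the seasons. It names only the peak malaria months, from Kiang West records.
- *A third of the trial takes iron in a peak month.* A third is on study product; about 22% would be on iron.

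**Conclusion.** The contradiction stands within the latest version. The timing safeguard in Sections 1.4.1 and 11.1.3 does not hold for cohort 3: 235 children, about 157 of them on iron, each with 33% to 37% of dosing days in October 2018. The figures assume that cohort 3 enrols in full, that it follows the Appendix 1 dates, that dosing is daily without early stopping, and that allocation is even within the cohort. Dropout would lower the counts and leave the conflict as it is.

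This is more than a clerical matter, because the sentence states a safety protection for children aged 6 to 35 months. Only that one protection fails, and no bias in the randomised comparison follows from it.

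**What to change.** 1. Reconcile Sections 1.4.1 and 11.1.3 with Appendix 1, including the 2017 limit, and put the reconciled text to the DSMB and ethics committee before cohort 3 dosing begins on 6 August 2018. Whether the text or the schedule should change is for the sponsor and those bodies; this review takes no position. The documentary cost is a short correction; any operational cost depends on how the passages are reconciled.

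2. As a secondary step, give the DSMB RDT-positive malaria and SAE counts by arm within cohort at the meeting that covers cohort 3. Section 6.1 already proposes review of adverse-event rates by arm, so this adds one table.

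3. In the analysis plan, include cohort in the models, since randomisation and the haemoglobin median split are done cohort by cohort. The purpose is precision and a view of any seasonal difference; it is not needed to remove bias. The cost is two indicator terms per model.
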